# Study design

## Study type and measurement

The study will be designed as randomized controlled trial. The primary outcome measurements will be the CR (percentage of children with egg counts >0 before treatment who become negative after treatment; e.g. the reduction in prevalence in the participants following treatment, calculated on a per-species basis and not taking into account the influence of the treatment on any co-infections) and the ERR (the reduction in egg count in a measured quantity of feces following treatment in those not cured; calculations based on the arithmetic mean egg count of the Kato-Katz slides prepared before and after treatment) revealed with the Kato-Katz method and achieved by treatment with any drug regimen for any soil-transmitted helminth species. The CR will be calculated using the formula ((N+/n) – (N3+/n))/(N+/n), where N+ is the number of positive children at baseline, N3+ is the number of children positive 3-4 weeks after treatment, and n is the total number of children with stool samples from both day 0 and 3-4 weeks post-treatment. The ERR induced by the treatment will be calculated as 100(1 – exp (-D))%, where D will be the mean difference (D = loge(c0+1) – loge(c1+1), where c0 is the egg count before treatment and c1 the egg count after treatment) for a particular treatment.

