# Patient inclusion and exclusion and withdrawal criteria

## Patient inclusion criteria

1. Age ≥5 years, both sexes.
2. Submission of 1 stool sample of sufficient size to perform a total of 2 thick Kato-Katz smears at the baseline parasitological survey.
3. Submission of 1 stool sample of sufficient size to perform a total of 2 thick Kato-Katz smears at the day of treatment.
4. Infection with *T. trichiura* as determined with the Kato-Katz method at the baseline survey. Additionally, also children with *A. lumbricoides* and/or hookworm infections will be included in one of the 4 treatment arms.
5. For females, not pregnant, as verbally assessed by medical personnel on the day of treatment.
6. Absence of major systemic illnesses, as assessed by medical personnel on the day of treatment.
7. No anthelminthic treatment in the past 4 weeks, as verbally confirmed by the participant at the baseline survey.
8. Written informed consent by the parent/legal guardian.

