# Study and treatment protocol

## Field procedures

The headmasters of the schools will be informed about the purpose and procedures of the study. Once informed consent is obtained, the objectives and procedures will be explained to the teachers, schoolchildren and their parents and written informed consent (see Appendix 1) by the participants’ parents/legal guardians will be obtained.

Field procedures are as follows. The study will be conducted between March and May 2009 (for exact protocol see Appendix 2). In an in-depth baseline survey before treatment, approximately 2000 children will be asked to submit 1 stool sample of sufficient size (at least 5 g) to perform the anticipated examinations. On the first day of the survey, about 200 participants will be given a plastic container and invited to bring a fresh stool specimen the following morning. Upon collection, a unique identification number will be attached to the container and demographic data will be collected (e.g., age and sex).

This procedure will be repeated over several days, entering ~200 additional schoolchildren every day up to a total of 2000 children. One of the inclusion criteria for the randomized drug trial is an infection with *T. trichiura* (see point 5.). We anticipate that with an expected prevalence of 25% of *T. trichiura* infections and with a compliance of 95% working for 2-3 weeks in Kinyasini and Chaani schools will suffice to obtain the required sample size of at least 540 children infected with *T. trichiura*. In addition those children diagnosed with *A. lumbricoides* and/or hookworm will also be attributed to one of the 4 treatment regimens, but their numbers are not included into the sample size calculations. Before the onset of the trial, each individual included into the trial will be physically examined by a medical assistant for exclusion criteria.

Once all samples have been collected and analysed, a randomized treatment list allocating the IDs of the ~540 children infected with *T. trichiura* and of the remaining children infected with *A. lumbricoides* and/or hookworm to one of the 4 treatment regimens will be prepared. On the day before treatment the selected children will be given another stool container and they will be asked to provide another stool sample the following morning. On the day of treatment the stool samples will be collected and all children’s weights will be recorded. The children will be allocated to one of four groups, as follows:

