**Week 11 and 12**

- Examine the SAF preserved stool samples from the days of follow up with the FLOTAC method

Laboratory procedures:

Kato-Katz slide

- Prepare 2 Kato-Katz slides from every stool sample (baseline screening, day of treatment, days of follow up)

- Read for hookworm within 20-30 minutes (hookworm eggs clear fast). Other eggs can be read later. Magnification: 100x

- Keep slides for quality control

- Count all eggs, no estimation after partial reading

- Record result on form

- 10% of slides are re-read by senior technician for quality control

SAF conservation

- Label tube containing 10 ml SAF solution with ID

- Fill 1-2 g stool into the tube

- Mix well

FLOTAC

- Pass SAF preserved stool through an aperture with 350 µm in order to remove large fibres

- Add 10 ml of SAF to 1 g of stool

- Pipette this stool-SAF suspension into a 15 ml Falcon tube

- Centrifuge for 3 min at 170 g

- Discard supernatant

- Fill tube to the 6 ml mark with S4

- Mix pellet accurately and transfer 5 ml into one of the two chambers of the FLOTAC apparatus

- Record which sample was filled into which chamber of which apparatus

- Centrifuge apparatus for 5 min at 120 g

- Translate the top portion of the flotation chambers and remove rest of apparatus

- Read observation grids at a 100x magnification

- Record and count helminth eggs separately for each species

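### As defined, the egg reduction rate does not give an interpretable absolute reduction: baseline slides, unit, type of mean and population need to be settled

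*Combined protocol and SAP*

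**What the plan says.** The section on study type and measurement names two primary outcomes, the cure rate (CR) and the ERR. It describes the ERR as "the reduction in egg count in a measured quantity of feces following treatment in those not cured", with "calculations based on the arithmetic mean egg count of the Kato-Katz slides prepared before and after treatment". The formula follows: "The ERR induced by the treatment will be calculated as 100(1 – exp (-D))%, where D will be the mean difference". D is the mean of loge(c0+1) – loge(c1+1), "where c0 is the egg count before treatment and c1 the egg count after treatment".

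Two stool samples precede treatment. The first is the screening sample, and entry depends on it: "Infection with *T. trichiura* as determined with the Kato-Katz method at the baseline survey". Field procedures repeats this. The second is described in the inclusion criteria as "Submission of 1 stool sample of sufficient size to perform a total of 2 thick Kato-Katz smears at the day of treatment"; it has to be submitted but need not be positive. Appendix 3 calls for two slides from every sample, so there are four slides before treatment and, with two follow-up samples, four after.

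No section says which pre-treatment slides form c0. Day 0 is mentioned only in the definition of n for the CR. No section says that c0 and c1 are converted to EPG. Objective 2 compares current efficacy against *A. lumbricoides* and hookworm with reports from Zanzibar in the 1990s.

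**The concern.** There are four problems in this one definition.

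1. **Baseline.** If c0 averages all pre-treatment slides, it includes the slides on which the child was selected. Egg counts vary from day to day, so a sample chosen for being positive tends to be followed by lower counts, treated or not.
2. **Unit.** Adding 1 matters little at hundreds of EPG and a great deal at a few eggs per slide. Without a stated unit, two analysts can report different primary results from the same data.
3. **Type of mean.** Averaging logs across children gives a geometric-type reduction, while the description speaks of an arithmetic mean.
4. **Population.** Being uncured is known only after treatment, so restricting the ERR to uncured children is selection on the outcome.

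What is at stake is the absolute ERR of each arm, and any ERR comparison with 1990s values under Objective 2. Randomisation does not protect that comparison.

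**Working it through.** **The plan's own figure.** The plan states no expected ERR for its arms. Its sample size rests on CR and reproduces. At 45% versus 65%, 7.85 × (0.45 × 0.55 + 0.65 × 0.35)/0.20² + 2/0.20 + 2 = 93.2 + 10 + 2 = 105.2, against the stated 105 per group. The ERR definition does not enter it.

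**Inputs.** A smear is 41.7 mg (Laboratory procedures), so 1 egg per slide is 24 EPG. In 2007, 25.9% of children were positive for *T. trichiura* on one sample and 47.9% on three (Sample size). Since 25.9/47.9 = 54%, one sample found only about half of the children found by three, so sample-to-sample variation is large.

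**Baseline slides.** Several simulations were calibrated to 25.9% and 47.9%. They selected children on a positive screening sample, took c0 as the mean of the screening and day-of-treatment slides and c1 as the mean of the follow-up slides, and set the drug effect to zero. The assumptions were lognormal intensity, lognormal or gamma day-to-day variation, an infected share that the documents do not give (80% in one set), and one or two slides per sample in the 2007 survey.

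| Spurious ERR, no drug effect | Those not cured | All enrolled |
|---|---|---|
| Log formula on slide counts | about 4–7% | 12–20% |
| Arithmetic means | about 2–11% | 5–30% |

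With heavier infections (an assumed median of 15 eggs per slide) the figures fall to about 1–2%.

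**Unit.** For one child the formula gives 1 – (c1+1)/(c0+1).

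| Eggs per slide | True fall | On slide counts | On EPG |
|---|---|---|---|
| 4 to 1 | 75% | 1 – 2/5 = 60.0% | 1 – 25/97 = 74.2% |
| 2 to 0.5 | 75% | 1 – 1.5/3 = 50.0% | 1 – 13/49 = 73.5% |
| 50 to 10 | 80% | 1 – 11/51 = 78.4% | 1 – 241/1201 = 79.9% |

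In the simulations a true 80% fall, scored on slide counts in those not cured, came out at 48–56% in one set of runs and 30–43% in another. With the heavier infections it came out at about 72%.

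**Type of mean.** Take two uncured children going from 10 to 1 and from 40 to 30 eggs per slide. D = [ln(11/2) + ln(41/31)]/2 = (1.705 + 0.280)/2 = 0.992, so the ERR is 1 – exp(–0.992) = 63%. By arithmetic means it is 1 – 31/50 = 38%.

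**Population and remedy.** With only the day-of-treatment slides as c0 and arithmetic means over all enrolled children, the simulated ERR was within about 1 percentage point of zero at no effect, 46–52% at a true 50%, and 79–83% at a true 80%. In those not cured, the same baseline gave about –2.5% to –24% at no effect. The restriction therefore has to go together with the change of baseline.

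**Log formula with unequal slide numbers.** Two day-of-treatment slides against four follow-up slides gave –10% to –18% at no effect on slide counts, and about –45% to –78% on EPG, in all children. Averaging more slides leaves fewer zeros after treatment and raises the mean log. With two slides on each side the slide-count result was –0.1% to 0.6%.

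**The case against.** The strongest reply is that much of this is ambiguity, not a wrong choice. The plan never lists the slides in c0. It speaks of a measured quantity of faeces, and its background section expresses intensity as EPG. The arithmetic mean may refer only to averaging one child's slides. All of this is fair, and on the last reading the text and the formula are consistent. But the formula then remains geometric across children, and the literal text still leaves the slides and the unit open for a primary outcome.

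Several stronger readings are tempting and are not supported:

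- A reader might infer that full clearance of a light infection scores far below 100% (4 to 0 eggs gives 80%, 10 to 0 gives 91%). Those children are cured and lie outside the ERR as defined. The understatement has to be shown in uncured children, as above.
- A reader might quote the all-enrolled artefacts of 12–20% and 5–30% as the bias in the plan's endpoint. In the defined population they are roughly 4–7% and 2–11%.
- A reader might conclude that Objective 2 fails, *T. trichiura* included. That objective covers only *A. lumbricoides* and hookworm and speaks of efficacy without naming ERR. Selection for these species depends on how each child entered, and the simulations do not quantify it. The documents also do not say how the 1990s ERRs were computed.
- A reader might infer a bias in one known direction. Selected baseline slides push the ERR up and the +1 on small counts pushes it down. The net sign depends on infection intensity, which the documents do not give.

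**Conclusion.** The concern holds in this form: followed literally, the definition does not yield an interpretable absolute ERR. Selection on the screening slides alone adds about 4–7% (log formula) or 2–11% (arithmetic means) in those not cured when the drug does nothing. Using slide counts in log(c+1) lowers a true 75% fall from 4 to 1 egg to 60%. The geometric and arithmetic versions can differ as widely as 63% and 38%. The simulated sizes apply to *T. trichiura*, rest on the distributional assumptions listed, and shrink with heavier infections.

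Contrasts between arms are less affected, because selection at screening precedes randomisation and acts alike on all arms. They are not wholly immune, since restriction to uncured children keeps a different subset where cure rates differ; that effect was not quantified. The sample size is unaffected. The definition should be corrected, but this does not undermine the trial's design.

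**What to change.** Rewrite the ERR definition so that it states four things.

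- **Slides:** c0 is the mean of the two day-of-treatment slides, which play no part in selection, and c1 is the mean of the follow-up slides.
- **Unit:** EPG, that is, eggs per slide × 24.
- **Formula:** ERR = 100 × (1 – arithmetic mean EPG after / arithmetic mean EPG before), with a bootstrap confidence interval.
- **Population:** all enrolled children positive for that species at screening, cured children included.

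If the log formula is kept as a secondary analysis, state its unit and use equal numbers of slides before and after (two versus two).

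The cost is wording and analysis code; no extra sampling is needed. The drawback is a noisier baseline, from two slides instead of four.

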**Table 1: Cure rates for *T. trichiura***

**Treatment A (albendazole or mebendazole)**

| **Treatment B**  **(albendazole or mebendazole plus ivermectin)** | 15% | 20% | 30% | 35% | 40% | 45% | 50% | 55% |
| --- | --- | --- | --- | --- | --- | --- | --- | --- |
| 60% | 21 | 27 | 48 | 69 | 106 | 185 | 407 | 1573 |
| 65% | 17 | 21 | 36 | 48 | 69 | 105 | 182 | 395 |
| 70% | 14 | 18 | 28 | 36 | 48 | 67 | 102 | 175 |
| 75% | 12 | 15 | 22 | 27 | 35 | 47 | 65 | 97 |
| 80% | 10 | 12 | 18 | 21 | 27 | 34 | 44 | 61 |
| 85% | 9 | 10 | 14 | 17 | 21 | 25 | 32 | 41 |
| 90% | 8 | 9 | 12 | 14 | 16 | 20 | 24 | 29 |

Based on the given information we estimate the CR of albendazole/mebendazole for *T. trichiura* infections to be between 20% and 45% and the CR of the combination of albendazole/mebendazole plus ivermectin to be between 65% and 80%. Hence, a sample size of at least 105 participants per treatment group is needed for significance analysis.

In the proposed study sites, the prevalence of *T. trichiura* infections is most likely to be above 30% and the compliance is estimated to be around 90%. These assumptions are based on a study performed in Kinyasini and Chaani schools in 2007 where 25.9% of the children were found to be infected with *T. trichiura* after examination of 1 stool sample and 47.9% after examination of 3 stool samples with the Kato-Katz method and where the compliance to submit 1-3 stool samples was >85%. In view of the required number of cases per group, and allocating for patients lost to follow-up, at least 2000 subjects would have to be screened so that 500-600 infected individuals infected with *T. trichiura* can enter the trial (see Appendix 5).

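### The cure-rate formula computes a net fall in prevalence, not the cure rate the protocol defines, and understates that cure rate whenever a child negative before treatment is positive at follow-up

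*Combined protocol and SAP*

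**What the plan says.** The section on study type and measurement gives two verbal descriptions of the CR and treats them as the same. The first is "percentage of children with egg counts >0 before treatment who become negative after treatment". The second is "e.g. the reduction in prevalence in the participants following treatment". The calculation follows: "The CR will be calculated using the formula ((N+/n) – (N3+/n))/(N+/n), where N+ is the number of positive children at baseline". The remaining two terms are set out thus: "N3+ is the number of children positive 3-4 weeks after treatment, and n is the total number of children with stool samples", the samples being those of day 0 and of follow-up. Neither term is limited to children who were positive before treatment. The measure is to be reported as "achieved by treatment with any drug regimen for any soil-transmitted helminth species".

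The inclusion criteria, the field procedures and Appendix 3 (Weeks 5 and 6) place children who carry only A. lumbricoides and/or hookworm in the same four arms as the T. trichiura-positive children. Each child gives one stool at screening, one on the day of treatment and two at follow-up, with two Kato-Katz smears per stool.

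**The concern.** The two descriptions coincide only if no child who was negative for the species before treatment is positive for it afterwards. The formula implements the second, net description, so each such child cancels a genuine cure in the count.

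New positives are to be expected because one stool misses many infections. In the 2007 survey of these schools, "25.9% of the children were found to be infected with" T. trichiura on one stool, against 47.9% on three. An infection missed before treatment and not cured can then be found on the two follow-up stools.

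Two uses of the CR are at stake. One is the comparison between arms: missed infections survive more often under the weaker drug, so its CR is lowered more. The other is Objective 2, which compares current A. lumbricoides and hookworm efficacy with values from the 1990s to look for resistance. A mechanically lowered CR points in the same direction as resistance.

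**Working it through.** **The plan's own figure.** The documents contain no trial CR to reproduce. The one planned figure built on CRs is 105 per group for 45% versus 65%. The protocol's equation gives 7.85 × (0.45×0.55 + 0.65×0.35)/0.20² + 2/0.20 + 2 = 93.2 + 10 + 2 = 105.2. It reproduces, and this point does not change it.

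**Algebra.** Write N3+ = a + b, where a is baseline positives still positive and b is baseline negatives now positive.
- Formula: 1 − (a + b)/N+.
- Stated definition: 1 − a/N+.
- Understatement: b/N+.

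Suppose a share m of baseline negatives are missed infections, cured at the same rate as detected ones and otherwise found at follow-up. With r baseline negatives per baseline positive, the understatement is r × m × (1 − CR).

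**Inputs for r.** 1800 screened and T. trichiura 30% (Appendix 8 flowchart); hookworm 22.5% and A. lumbricoides 16.5% (Study area and population surveyed). Assume independent infections and that every infected child enters.
- Any infection: 1 − 0.70 × 0.835 × 0.775 = 0.547, or about 985 children.
- Hookworm: r = (0.547 − 0.225)/0.225 = 1.43.
- A. lumbricoides: r = (0.547 − 0.165)/0.165 = 2.32.

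**Result**, with true CRs from the Sample size section:

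| Species and drug | True CR | m = 5% | m = 10% | m = 20% |
|---|---|---|---|---|
| Hookworm, mebendazole | 15% | 8.9% | 2.8% | −9.3% |
| Hookworm, albendazole | 72% | 70.0% | 68.0% | 64.0% |
| A. lumbricoides, albendazole | 88% | 86.6% | 85.2% | 82.4% |

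For example, hookworm on mebendazole at m = 10%: 1.43 × 0.10 × 0.85 = 12.2 points. A negative value is impossible for a share of children cured. At the 98.9% A. lumbricoides CR reported from Pemba in 1992/93, m = 10% costs 2.32 × 0.10 × 0.011, or about 0.3 points.

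**Arm contrast.** For hookworm at m = 10%, a true albendazole–mebendazole difference of 72 − 15 = 57 points would be reported as 68.0 − 2.8 = 65.2.

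**Objective 2.** The 1992/93 hookworm CRs were 56.8% (albendazole) and 22.4% (mebendazole). If efficacy were unchanged, m = 10% would give 56.8 − 1.43×0.10×43.2 = 50.6% and 22.4 − 1.43×0.10×77.6 = 11.3%.

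**Sensitivity to r.** If the species overlapped completely, only the 30% with T. trichiura would be infected. Hookworm r would be (0.30 − 0.225)/0.225 = 0.33, and the mebendazole fall at m = 10% would be 0.33 × 0.10 × 0.85 = 2.8 points rather than 12.2.

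**T. trichiura.** The flowchart's CR boxes hold 103 children per arm (135 − 7 − 14 − 11), all positive at screening. If screening defines baseline, b = 0 and the formula is exact. New positives arise only if the other-species children are counted, or if the day-0 stool alone defines baseline and some screen-positive children are negative on that day.

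**The case against.** The best defence is that the first description already states the right quantity, so an analyst would naturally restrict both counts to children positive before treatment. That is a possible intention, but the formula does not express it. In a set of baseline positives N+ equals n, and dividing by n would serve no purpose. The text also offers the prevalence reading as equivalent.

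Three limits on size stand.

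- **A. lumbricoides.** A reader might assume that 3% to 10% of baseline negatives turn positive and infer a fall of about 7 to 23 points (2.32 × 3% to 2.32 × 10%), enough to imitate resistance. Missed infections cannot do this at the 1992/93 cure rate. At 98.9%, at most 1.1% of negatives could remain positive even if all were infected, a fall of no more than 2.32 × 1.1 = 2.5 points. Only new infection within three to four weeks could add more, and the documents give no rate for it.
- **T. trichiura.** A reader might take the 2007 missed share, (47.9 − 25.9)/(100 − 25.9) = 29.7%, and infer that a CR of 28% would be reported as about 10%. That requires adding the other-species children to the calculation, whereas the flowchart shows the CR only in screen-positive children. It also ignores the second pre-treatment stool. If both stools define baseline, with equal and independent sensitivity per stool, the share falls to about 20%.
- **Independence.** The background section describes multiple-species infection as the rule. Positive association lowers r, so 1.43 and 2.32 are probably on the high side.

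Finally, the documents do not say how the 1990s comparison rates were calculated, so the net effect on Objective 2 cannot be fixed from them.

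**Conclusion.** The point holds. One primary outcome carries two definitions that are not equivalent, and the formula follows the one that is not a cure rate. The understatement is exactly b/N+. Under missed infections with equal cure rates it grows with 1 − CR. It is therefore larger in the less effective arm and greatest for hookworm on mebendazole: about 12 points at m = 10% with independent infections, about 3 points with complete overlap. It is about 4 points for hookworm on albendazole and about 3 points for A. lumbricoides at a CR of 88%, both at m = 10% with independent infections.

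These sizes are illustrations. The documents give neither m nor the number of children with other species only. The algebra needs no assumption. The T. trichiura comparison is unaffected in the flowchart set with screening as baseline; the protocol does not settle that condition, since it ties n to day 0.

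**What to change.** Replace the formula, for each species, with: CR = (children positive before treatment and negative at follow-up) / (children positive before treatment who have a follow-up sample). State whether the screening stool, the day-0 stool or both define positive before treatment. Report children negative before and positive after on a separate line by arm.

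The explicit denominator also closes a smaller gap: N+ is not expressly limited to children with paired samples. If it covered everyone treated, children lost to follow-up would count as cured. With 114 positive, 103 followed and, for illustration, 57 still positive, the formula gives 1 − 57/114 = 50.0% instead of 1 − 57/103 = 44.7%.

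The cost is one formula and two sentences. No new data are needed and the sample size is unchanged. It should be settled before the analysis, so that the choice of definition cannot depend on the results.
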